### Intervention description {11a}

This study comprises two sub-studies, each designed as a two-arm trial. The participants are classified into sub-studies based on their functional reserves as follows:Motor priority group (sub-study 1): Patients with well-preserved motor function in whom motor skills have a significant impact on overall functioning; andCognitive priority group (sub-study 2): Patients with well-preserved cognitive function and notable impairment in motor function in which cognitive abilities substantially affect overall functioning.

As part of the pre-intervention assessment, the TUG and the TUG under cognitive dual-task condition (TUG-Cog) are administered. The TUG-Cog involves performing the TUG test concurrently with a cognitive task of serially subtracting the number 3. Additionally, serial 3 subtraction as a single cognitive task is performed from a randomly selected number between 80 and 100 for 20 s in the sitting position [34]. For both tasks, the correct response rate for subtraction is calculated as the time spent in seconds divided by the number of correct responses. Task-specific interference is calculated using the equation for dual-task effect (DTE) (Eq. 1) [37]. The motor dual-task effect (mDTE) is computed using stride length and the cognitive dual-task effect (cogDTE) is based on the correct response rate of TUG and TUG-Cog.1$$\text{Dual task effect} \left(\%\right)=\frac{(\text{Single task }-\text{ Dual task})}{\text{Single task}} \times 100$$

For evaluation of task prioritization during dual-task conditions, the modified Attention Allocation Index (mAAI) is employed (Eq. 2) [34]. The mAAI is calculated by subtracting the cogDTE from the mDTE, where negative values indicate an attention shift toward the motor task (motor priority), while positive values suggest an attention shift toward the cognitive task (cognitive priority).2$$\text{modified Attention Allocation Index }\left(\text{mAAI}\right)=\text{motor dual task effect}\left(\text{mDTE}\right)-\text{cognitive dual task effect }(\text{cogDTE})$$

Patients demonstrating motor priority will undergo high-frequency rTMS over the primary motor cortex in the lower limb (M1-LL), whereas those showing cognitive priority receive high-frequency rTMS over the left DLPFC. Given the substantial impairment of the motor network in the latter group, we envision a heightened reinforcement of compensatory mechanisms utilizing the cognitive network.

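### As printed, the correct response rate is seconds per correct response, so the mAAI adds the motor and cognitive losses instead of contrasting them

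*Protocol article*

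**What the plan says.** All the elements stand in the Protocol article, Intervention description {11a}.

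- The cognitive measure: "the correct response rate for subtraction is calculated as the time spent in seconds divided by the number of correct responses".
- One formula for both domains: "Task-specific interference is calculated using the equation for dual-task effect (DTE) (Eq. 1"), where Eq. 1 is (single − dual)/single × 100.
- The motor input: "The motor dual-task effect (mDTE) is computed using stride length".
- The cognitive input: "the cognitive dual-task effect (cogDTE) is based on the correct response rate of TUG and TUG-Cog".
- The index: "The mAAI is calculated by subtracting the cogDTE from the mDTE" (Eq. 2).
- Its reading: "negative values indicate an attention shift toward the motor task (motor priority") and "positive values suggest an attention shift toward the cognitive task (cognitive priority").

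The sign of the mAAI is the only numerical rule given for entry to sub-study 1 (motor priority, experimental target M1-LL) or sub-study 2 (cognitive priority, experimental target left DLPFC). The Abstract names the correct response rate without a formula. Outcomes {12} confirms that stride length is used to assign sub-studies. No section gives a sign reversal or another definition.

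**The concern.** A contrast of two dual-task effects can be read as prioritisation only if both are coded in the same direction. Stride length is better when higher, so Eq. 1 makes a loss positive. Seconds per correct response is worse when higher, so Eq. 1 makes a loss negative. Subtracting a negative loss adds it. The index then measures something close to total dual-task cost, and the stated reading of its sign no longer follows.

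At stake is who enters which sub-study. The trial's hypothesis is that stimulation matched to functional reserve improves ambulation. If the index that determines reserve does not separate the two kinds of patient, each sub-study tests its target in a population other than the one described.

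There are two smaller defects in the same definition. Seconds per correct response is undefined for a patient who gives no correct response. The sentence on cogDTE also names the TUG as one source of the rate, although the TUG alone contains no subtraction; the only single-task subtraction described is the seated 20-s test.

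**Working it through.** The protocol states no figure for this point, so there is none to reproduce. The check is algebra on Eq. 1 and Eq. 2, followed by examples.

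**Algebra.** Let m be the fractional loss of stride length, and c the fractional loss in correct responses per second (c < 1).

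1. mDTE = m.
2. With correct responses per second, cogDTE = c and mAAI = m − c. This is negative when the cognitive loss is the larger, which matches the stated reading (motor priority).
3. With seconds per correct response, the dual-task value is the single-task value divided by (1 − c). Hence cogDTE = 1 − 1/(1 − c) = −c/(1 − c), and mAAI = m + c/(1 − c).
4. If m > 0 and 0 < c < 1, both terms in step 3 are positive. Such a patient is always classed as cognitive priority, and more firmly so the more the subtraction suffers.

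**Examples** (patient values assumed; stride in m, subtraction in correct/s; effects in %).

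| Stride | Subtraction | mDTE | cogDTE as printed | mAAI as printed | cogDTE, correct/s | mAAI, correct/s |
|---|---|---|---|---|---|---|
| 1.00 → 1.00 | 0.50 → 0.25 | 0 | (2 − 4)/2 = −100 | +100 | +50 | −50 |
| 1.00 → 0.90 | 0.50 → 0.40 | +10 | (2 − 2.5)/2 = −25 | +35 | +20 | −10 |
| 1.00 → 0.90 | 10 in 20 s → 4 in 12 s | +10 | (2 − 3)/2 = −50 | +60 | +33.3 | −23.3 |
| 1.00 → 0.90 | 10 in 20 s → 6 in 10 s | +10 | (2 − 1.67)/2 = +16.7 | −6.7 | −20 | +30 |

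The classification flips in every row. In the first, the patient protects gait and halves subtraction, yet is labelled cognitive priority. The last row shows the reverse error: subtraction improves while stride shortens, and the printed index says motor priority.

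**How many patients.** The protocol gives no distribution of either effect, so any share rests on assumptions. I took independent normal effects with mean motor cost 5, 10 or 15% (SD 5 or 10) and mean cognitive cost 0, 10 or 20% (SD 15 or 25), the cognitive cost capped at 95%, with 400,000 simulated patients per combination.

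- The two definitions disagree for 31% of patients (motor 15, SD 5; cognitive 0, SD 15) to 87% (motor 5, SD 5; cognitive 20, SD 15).
- Of those who are motor priority on correct responses per second, 76–100% are relabelled.
- Of those with a loss on both tasks, none is classed as motor priority in any combination, as step 4 requires.

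**The case against.** The strongest reply is that this is a slip in the article. The quantity is called a rate, and the sign rule fits correct responses per second, so numerator and denominator may simply have been transposed in print while the trial computes the right ratio. That is plausible, and the document cannot exclude it. It does not remove the contradiction, because the published rule cannot be followed to its stated meaning. It does make any misrouting conditional.

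A reader might infer more than the text supports, in four ways.

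- That patients have already been misrouted. The protocol does not show which ratio was computed.
- That every misclassified patient gets a different target. Control patients receive bilateral M1-UL in both sub-studies, and allocation is 1:1, so only about half could be affected in that way.
- That neither sub-study is valid. Randomisation takes place within each sub-study and no comparison between them is planned, so each comparison stays internally valid. What fails is the description of the population and the hypothesis tied to it.
- That the motor sub-study could not be filled. This depends on the mean cognitive cost. At zero mean cost the motor share can barely move (37.6% to 36.5% with motor 5, SD 5 and cognitive SD 15). It falls sharply only when the mean cognitive cost is clearly positive.

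The remark about the TUG as single task is minor taken alone, since the seated subtraction is introduced as the single cognitive task just before. It is worth correcting in the same sentence.

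**Conclusion.** The definition, Eq. 1 and the sign rule contradict one another, and no other section repairs this. One consequence is certain and needs no distributional assumption: under the printed text a loss on both tasks can never give motor priority. The share of patients whose sub-study would change is not known; 31–87% is a range under assumed distributions and should not be quoted as an estimate for this trial. Whether anyone has been misassigned depends on whether the trial computes the printed ratio. This must be settled, because the mAAI sign alone decides sub-study entry and, in the experimental arms, the target. According to Trial status, the study started on 20 February 2024.

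**What to change.** 1. Reconcile the definition, Eq. 1 and the sign rule. The simplest way is to define the correct response rate as the number of correct responses divided by seconds. The equations and the stated reading then agree, and no correct response in the TUG-Cog gives cogDTE = 100%, provided that the seated test produced at least one. Keeping seconds per correct response and reversing the sign of cogDTE also restores the reading, and classifies about 1–6% of patients differently from the first repair on the same assumed grid. It leaves the zero-response case undefined.
2. Name the seated 20-s subtraction as the single task and the TUG-Cog as the dual task for cogDTE.
3. Confirm which ratio has actually been computed for sub-study assignment. If it is already correct responses per second, a correction to the text is enough.
4. If it is the printed ratio, correct it for future assignments, recompute the mAAI from the recorded data for everyone enrolled, and report how many would change sub-study. Keep the randomised comparisons as conducted, and add a sensitivity analysis by corrected classification. It may leave few patients: with 30 per sub-study and changes spread evenly, 31–87% reclassified leaves about 30 × 0.69 = 21 down to 30 × 0.13 = 4.

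The cost is a short amendment and, if needed, a recalculation from times, response counts and stride lengths already collected. No new measurement is required.

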### Criteria for discontinuing or modifying allocated interventions {11b}

The criteria for discontinuing the intervention are as follows:Voluntary discontinuation by the participant: Participants have the freedom to withdraw from the trial at any time without providing an explanation, and this will not affect their future treatment.Missed follow-up visits.Discontinuation due to a significant adverse event or if the participant or legal representative requests termination due to adverse events.Based on the investigator’s judgment, the progression of a clinical trial may be deemed unsuitable.Significant protocol violation or deviation from inclusion/exclusion criteria during the clinical trial.Study adherence < 80%.$$\text{Adherence }\left({\%}\right)= \left(\frac{\text{Actual number of rTMS sessions performed}}{\text{Total required rTMS sessions}}\right)\times 100$$

Modifications of allocated interventions are not considered.

### Strategies to improve adherence to interventions {11c}

Stimulation protocols for all interventions have been already established for their effectiveness in patients with PD [9, 44]. Participants will be informed that, regardless of their assigned study group, they could expect to experience several known benefits of rTMS. Furthermore, given that all interventions will occur within the hospital, clinical research coordinators will maintain periodic contact through phone calls or text messages to remind the participants of upcoming interventions.

### Relevant concomitant care permitted or prohibited during the trial {11d}

Participants are required to maintain a consistent dosage of their antiparkinsonian medication throughout the study. In addition, the same dose of physical therapy is permitted. Any changes are prohibited.

### Provisions for post-trial care {30}

In this study, participants will receive compensation through the clinical trial insurance coverage held by the investigator in adherence to the study’s victim compensation protocol. This coverage extends to physical damage incurred as a result of the investigational medical device and any adverse, unintended reactions arising from the study procedures. Nevertheless, compensation is not applicable in scenarios where the investigational medical device fails to yield valid results or prove beneficial, or in cases of damage resulting from negligence on the part of the participant, among other specified exclusions.

### Outcomes {12}

Pre-intervention evaluations will be conducted within 3 days before the initial intervention session. Post-intervention evaluations will be conducted within 48 h after the final intervention session. Follow-up evaluations will be conducted 2 months after the intervention concludes. The primary outcome is the difference in TUG time between the pre- and post-intervention evaluations. Secondary outcome variables include the TUG measured at follow-up evaluations. Additionally, the TUG-Cog, MDS-UPDRS Part III, New Freezing of Gait Questionnaire (NFoGQ), Digit Span, trail-making test, transcranial magnetic stimulation-induced motor-evoked potential (TMS-induced MEP), diffusion tensor imaging (DTI), and rsfMRI are assessed pre-intervention, post-intervention, and at follow-up to investigate the effectiveness of personalized rTMS.

The TUG assesses ambulatory functions, including gait, balance, mobility, and fall risk. In the TUG, the participants are instructed to rise from a chair, walk to a traffic cone located 3 m away at a comfortable pace, return to the chair, and sit down. The TUG-Cog involves the simultaneous execution of the TUG test and serial subtraction in three, starting from a randomly selected number between 80 and 100 [34]. The TUG-Cog is designed to provide a comprehensive assessment by incorporating both motor and cognitive tasks. The TUG and TUG-Cog are each measured twice, and the mean values are utilized for analysis. During the TUG and TUG-Cog, the participants wore shoes equipped with a smart insole (Gilon Gait Data Collector & Analyze MD, Gilon Inc., Gyeonggi, Republic of Korea). The smart insole measures gait parameters including stride length, step count, cadence, velocity, distance, swing ratio, and foot plantar pressure (heel/mid/toe). The stride lengths of the TUG and TUG-Cog are utilized to assign sub-studies and evaluate the efficacy of the intervention. During the mid-intervention evaluation, the TUG is conducted without smart insoles.

The MDS-UPDRS part III assesses the motor symptoms of PD using 18 items, with each item scored on a scale of 0 to 4 [46]. Higher scores indicate more severe symptoms. The NFoGQ consists of nine items designed to assess the severity of freezing of gait (FoG) and gait disturbance [47]. The NFoGQ has demonstrated reliability in measuring both the severity of FoG and its functional impact in patients with PD.

Cognitive function is assessed using the Digit Span and trail-making test. The Digit Span evaluates attention and working memory. Participants are instructed to repeat a sequence of numbers, either in the same order (forward) or in the reverse order (backward). The sequence starts with three numbers in the forward task and progresses to nine numbers, whereas the backward task involves sequences from two numbers up to eight numbers. The trail-making test evaluates cognitive functions, such as cognitive processing speed and executive function. In trail-making test A, the participant connects numbers from 1 to 15, while in trail-making test B, the task involves connecting eight numbers and seven letters (Monday to Sunday in Korean) in alternating ascending order. The examiner measures the time taken by the participants to complete the task.

Cortical excitability through TMS-induced MEP from the bilateral first dorsal interosseous muscles is utilized to evaluate the efficacy of the intervention. The intensity is set at 120% of the RMT at intervals of 5 s or more, and repeated 10 times. The average amplitude of the top five responses is measured and evaluated. Brain imaging data, including rsfMRI, DTI, and T1-weighted structural images, will be acquired using 3-T scanners (Philips Ingenia CX, Philips Elition, Siemens Magnetom Trio, and Siemens Magnetom Vida). rsfMRI will be utilized to extract brain networks based on their functional connectivity. Changes in brain network characteristics due to the intervention will be examined through connectivity strength, graph theory, and large-scale network analyses of global and local networks, as well as intrahemispheric and interhemispheric networks. During the resting-state scan, participants will be instructed to keep their eyes closed and remain motionless. A total of 180 whole-brain images will be collected at each session using the following metrics: 75 axial slices, slice thickness = 2 mm, no gap, matrix size = 112 × 112 or 124 × 124, and repetition time = 2000 ms. DTI will be employed to extract the integrity of major neural pathways and structural networks using fiber tractography and to examine changes in the characteristics of the integrity and networks due to the intervention. Each session will acquire more than 30 diffusion-weighted images with b = 1000 s/mm^2^, ensuring a minimum of 75 axial slices, a slice thickness = 2 mm, no gaps, and a matrix size of = 112 × 112 or 128 × 128. T1-weighted structural images will be used to determine the individual target positions in the DLPFC. The images will be acquired with a resolution and slice thickness of 1 mm or less, following the recommendations of the Neurophet software for 3D modeling-based target positioning.

All evaluations will be conducted in the “on” state, representing the peak effect of PD medication. Outcome measures will be assessed at pre-, post-intervention, and follow-up evaluations. Evaluation during the intervention will only proceed for the TUG, TUG-Cog, and TMS-induced MEP.

### Participant timeline {13}

Figure 1 presents a comprehensive flowchart of the study process, including the allocation phase. After enrollment and screening, a pre-intervention evaluation is conducted. Based on the pre-intervention evaluation, participants are classified into sub-studies and allocated to either the experimental or control group. The first rTMS session takes place within 3 days of the pre-intervention evaluation. The initial 5 interventions are administered within 2 weeks, with a mid-intervention evaluation employed within 24 h following the fifth session. Subsequently, an additional 5 rTMS sessions are administered over the next 2 weeks, and within 48 h of completing all intervention sessions, an immediate post-intervention evaluation is conducted. Follow-up evaluation is performed 2 months after the completion of the intervention, marking the end of the study. The total study duration is anticipated to be approximately 12–14 weeks. The timelines for both the experimental and control groups in the sub-studies are identical (Table 2).

**Fig. 1 Fig1:**
[figure not shown]
Flowchart through the entire study process *TUG* Timed-Up and Go, *TUG-Cog* Timed-Up and Go under cognitive dual-task condition, *UPDRS* Unified Parkinson’s Disease Rating Scale, *NFoGQ* New Freezing of Gait Questionnaire, *TMS-induced MEP* Transcranial magnetic stimulation-induced motor-evoked potential, *MRI* Magnetic resonance imaging, *rsfMRI* Resting state functional magnetic resonance imaging, *DTI* Diffusion tensor imaging

**Table 2 Tab2:** Schedule of enrollment, interventions, and assessments in the study

	**Study period**						
	**Enrollment**	**Baseline**	**Intervention**			**Post-intervention**	**Close-out (****2 months)**
**Timepoint**	*** − t***_***1***_	**t**_***0***_	***t***_***1–5***_	***t***_***6***_	***t***_***7–11***_	***t***_***12***_	***t***_***13***_
**Enrollment:**							
Informed consent	X						
Eligibility screen	X						
Allocation		X					
**Interventions:**							
* HF rTMS over M1-LL*			X		X		
* HF rTMS over DLPFC*			X		X		
* HF rTMS over bilateral M1-UL*			X		X		
**Assessments:**							
* TUG, TUG-Cog*		X		X		X	X
* Gait analysis*		X				X	X
* MDS-UPDRS Part III*		X				X	X
* NFoGQ*		X				X	X
* Cognitive function test*		X				X	X
* TMS-induced MEP*		X		X		X	X
* Brain MRI*		X				X	X
* Adverse event measure*		X	X	X	X	X	X

*HF rTMS* High-frequency repetitive transcranial magnetic stimulation, *M1-LL* Primary motor cortex in the lower limb, *DLPFC* Dorsolateral prefrontal cortex, *M1-UL* Primary motor cortex in the upper limb, *TUG* Timed-Up and Go, *TUG-Cog* Timed-Up and Gg under cognitive dual-task condition, *MDS-UPDRS* Movement Disorder Society-Unified Parkinson’s Disease Rating Scale, *NFoGQ* New Freezing of Gait Questionnaire, *TMS-induced MEP* Transcranial magnetic stimulation-induced motor-evoked potential, *MRI* Magnetic resonance imaging

### Sample size {14}

The primary outcome is the change in TUG time between pre- and post-intervention evaluations. The power of the study was set at 80%, with a significance level (α) of 5%. The clinically significant effect size (δ) was determined to be 4.9, and the expected standard deviation (σ) is estimated to be 4.0 [48, 49]. The analysis was conducted using Lehr’s formula, resulting in a required sample size of 10.6 [50].$$\text {Lehr's}\,\mathrm{formula}=\left(16/(\delta/\sigma)\right)=\left(16/(4.9/4.0)\right)^2=10.6$$

The follow-up rate was targeted at 75%, based on the conventional outpatient rehabilitation treatment criteria over a 4-week period. Therefore, the sample size for each sub-study was determined to be 30.

### Recruitment {15}

Study participants will be recruited by posting notices on the bulletin boards of respective 5 hospitals. The investigators will not exclude potential participants based on race or socioeconomic status. If eligible according to the study criteria, every effort will be made to facilitate the participation of eligible patients in this research. Additionally, patients will be informed about the purpose of the study to ensure representation of the entire PD patient population receiving treatment at each institution.

## Assignment of interventions: allocation

### Sequence generation {16a}

Participants are randomly allocated to the experimental and control groups of each sub-study. A designated individual, who is not involved in this study, utilizes the www.randomization.com to generate a randomization table, ensuring a 1:1 allocation between the experimental and control groups before the enrollment of the first participant. The chief investigator (CI) maintains the confidentiality of the randomization table matching list and refrains from revealing it until the completion of the final statistical analysis, managing it securely as per protocol.

### Concealment mechanism {16b}

The order of assignment is concealed using an electronic data capture system until each participant is assigned.

